**Fig. 2 Fig2:**
[figure not shown]
Timetable of sub-projects of the TCALL initiative

### Aims of “Center for Coordination and Transfer”

The “Center for Coordination and Transfer”, which is the subject of this study protocol, is responsible for the coordination, evaluation and dissemination of the overall TCALL initiative. It is made up of three main aspects (Fig. 3):

Strategic steering, including a legal report and development of a theoretical model for ATNH, Evaluation of the TCALL initiative and,Dissemination of innovations that have been tested in practice and, in the event of a positive assessment, implemented on a broad scale and thus achieve both care-related and scientific utilization.

The overall goal of these three aspects is to permanently consolidate the structures developed by the TCALL initiative on a national level by bringing together actors with similar interests on a political, scientific, economic and social level beyond the federal state of Bremen and its region. The assessment of the impact and measurability of the influences on care recipients and employees through an overall evaluation of the TCALL initiative is necessary, firstly, to draw scientific conclusions from the initiative, and, secondly, to legitimize the continuation of the initiative.

**Fig. 3 Fig3:**
[figure not shown]
Products of the sub-project Center for Coordination and Transfer

## Methods and analysis

### Strategic steering - Coordination

The “Center for Coordination and Transfer” is concerned with coordinating the various sub-projects of the TCALL initiative and aligning their content. Regular meetings are held for this purpose. In addition, it acts as a data management center and works closely with the Competence Center for Clinical Trials Bremen, which acts as a trust center for the data. As a result, all TCALL sub-projects can use the data in pseudonymized form. To provide strategic guidance, a model for the structure of ATNH will be developed and a legal report will be commissioned by a legal expert on what part of the legal framework needs to be adapted to allow for a nationwide rollout, which will serve as the basis for a nationwide rollout.

#### Data collection

The study protocol follows the SPIRIT reporting guidelines for study protocols for clinical trials. Outcomes will be measured with reliable, valid and pretested instruments (Table 1). Most used questionnaires are free to use and do not need any license except for “The Neuropsychiatric Inventory Nursing Home Version (NPI-NH)” and the *“*Adult Social Care Outcomes Toolkit (ASCOT-SCT4)”. Licenses in both cases were obtained and permission for use is confirmed. Ethical approval was confirmed by the ethics committee of the German Society of Nursing Science in October 4th, 2024. Baseline data collection in the intervention group started in November 11th, 2024 and is ongoing, follow-up data collection continues at six-month intervals, and the end of the first study phase is planned for 2027. Questionnaires for employees and residents are completed digitally, with the exception of the Adult Social Care Outcomes Toolkit (ASCOT-SCT4) [21], which is paper-based. Data collection of residents’ files, structural data of institutions and data from quality audits will be retrieved by the staff of the University of Bremen and the City University of Applied Sciences in Bremen. All data collection will take place in the intervention nursing homes and matched control groups. Data analysis is pseudonymized.

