
### Aims and structure of the TCALL initiative

The TCALL initiative is funded up to nine years by the German Federal Ministry of Research, Technology and Space and is a cooperation between the University of Bremen, the City University of Applied Science Bremen, the Integrated Health Campus Bremen and three nursing homes as practical partners (one from Johanniter and two from Caritas^2^). TCALL combines various sub-projects to achieve the vision of a Transfer Cluster of Academic Teaching Nursing Homes. This vision aims to create a direct transfer pathway from research via training to care – and vice versa, from care practice and the identification of problems back to research and training which address these problems. This is achieved by introducing innovations (social and technological) into LTC across the board and adapting internal work processes in LTC accordingly through personnel and organizational development, as well as further developed training content and structures. TCALL offers the opportunity to implement innovations directly in everyday care in the ATNH, which is not possible in conventional research projects and under laboratory conditions. These real-life conditions will also lead to feedback loop effects for science so that new and relevant research questions can be derived and tackled. In order to support these processes, special staff was hired and introduced in the three ATNH. These transformation and innovation agents (TIAs)^3^ are a special feature in the TCALL initiative, and they are responsible for a regular exchange between nursing homes and research partners. The TIAs form the interface to the ATNH and ensure a trustful cooperation. They will support all measures within TCALL to ensure that processes run smoothly and to reduce the workload of employees in the participating nursing homes.

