**Fig. 1 Fig1:**
[figure not shown]
Transfer path of TCALL

After a phase of planning and preparation in 2023 (start-up phase), the first sub-projects started in December 2023 and January 2024. The first one (Development of a decentralized learning infrastructure) aims to design and develop a learning infrastructure for LTC close to the workplace including a combination of different learning concepts. The second (Center for Coordination and Transfer), which is the subject of this study protocol, is responsible for the overall evaluation, strategic steering and dissemination of the entire TCALL initiative as well as for the development of strategies for a nationwide rollout.

Two more sub-projects started in 2024: “Digitalization and transfer of technical innovations in LTC” aims to select and test digital technologies, while “Competence-oriented work-organization” aims to implement new organizational and personnel structures in nursing homes based on the qualification levels of the employees. The objective of “Evidence-based Nursing” is the establishment of developed instruments and measures in the context of evidence-based nursing in participatory cooperation with the ATNH and is planned for the end of 2025. The timetable for all sub-projects in TCALL until the end of 2027 can be seen in Fig. 2.

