###### Indicators of a high workload

Due to the complex organizational change in staff, changes in indicators for a high workload, like sickness rate, staff turnover and the use of temporary employment agencies are expected at end of the study. To some extent, it is possible that during the restructuring process of staff deployment and shortly after implementation, the indicators for a high workload show an increase instead of a decrease. These non-intended effects are based on the fact that learning and getting used to new workflows initially leads to additional work and only later to positive effects (J-curve effect).

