#### Health economic evaluation

The health economic evaluation aims first, to calculate the expenses of the intervention and second, to relate the outcomes of the intervention to its costs (cost effectiveness analyses). In doing so, it is essential to distinguish between the costs of the interventions and the costs of the study, particularly the costs of the evaluation of the initiative. While TIAs are necessary for sustainable ATNH and the costs of ongoing innovations and their evaluation are also part of the intervention, the evaluation of the TCALL initiative as a whole and the dissemination are study costs, which have to be treated differently. For the measurement of effects data from the summative evaluation is used. Costs do not only include direct intervention costs, but also the costs of TIAs and all measures necessary for a sustainable structure of the ATNH. As far as outcomes can be measured in monetary terms (e.g., reduction in sickness rate) cost-benefit analyses are conducted from the perspective of the nursing home. With respect to the reduction of hospital admissions cost-benefit analyses from a societal perspective are added.

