#### Statistical analysis

The statistical analysis examines the changes in the outcomes in both groups, i.e., employees and residents, in t0 compared to t1-t6 and checks whether these changes differ between the intervention and control groups (difference-in-difference approach). Via correlation analyses we also analyze correlations between different outcome measures as e.g., job satisfaction and quality of care. Confounders will be controlled via regression analyses.

Information conducted within the formative evaluation especially from focus groups will be analyzed descriptively. Click rates and social media views are counted and analyzed with several digital analysis tools and programs to evaluate the dissemination activities.

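### Intervention-group t0 may already be partly exposed, yet it is the only reference for the difference-in-differences, so any effect present at t0 is subtracted from every later contrast

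*Protocol article*

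**What the plan says.** **Reference point.** The protocol article's Statistical analysis section examines changes "in t0 compared to t1-t6" and asks whether they differ between intervention and control homes. It names no earlier reference period for any outcome.

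**Timing of t0.** Data collection: "Baseline data collection in the intervention group started in November 11th, 2024 and is ongoing". Trial status adds that t0 was still open, and control homes still being recruited, when the article was submitted.

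**Timing of the initiative.** Aims and structure of the TCALL initiative (text after Fig. 1) treats 2023 as a preparatory year. It then says "the first sub-projects started in December 2023 and January 2024" (learning infrastructure; coordination and transfer) and "Two more sub-projects started in 2024" (digitalization; competence-oriented work organization). The fifth, Evidence-based Nursing, "is planned for the end of 2025".

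**TIAs.** The same section says "special staff was hired and introduced in the three ATNH", without a date. Health economic evaluation counts them on the intervention side: "TIAs are necessary for sustainable ATNH and the costs of ongoing innovations and their evaluation are also part of the intervention".

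**Expected early course.** Indicators of a high workload allows that, during and shortly after the restructuring of staff deployment, "the indicators for a high workload show an increase instead of a decrease". It calls this a J-curve. The indicators concerned are sickness rate, staff turnover and agency use.

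Strengths and limitations does not discuss the timing of the baseline.

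**The concern.** A difference-in-differences anchored at t0 estimates the effect of the initiative only if t0 shows both groups unexposed. Here the intervention homes may already have been changing when t0 was measured, while the control homes were not. The controls cannot correct for that, since they correct only for what both groups share. The issue is separate from matching and from whether earlier trends were parallel: with perfectly parallel trends, a t0 taken under exposure is still not a baseline.

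For the three workload indicators the article itself describes a mechanism that would flatter the result. If t0 falls in an early worsening, a return to the starting level counts as improvement over the control homes. Sickness rate also enters the planned cost-benefit analysis, and the overall evaluation is meant to justify continuing the initiative. In the other direction, a real gain already achieved by t0 would vanish from the estimate.

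**Working it through.** The article gives no sample size, effect size or standard deviation, so there is no figure of its own to reproduce. The check is date arithmetic followed by the expected value of the planned contrast.

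**1. Time from first sub-project starts to the opening of t0 (11 Nov 2024).** The text gives months only, so both ends of the range are shown, at 30.4375 days per month.

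- From 1 Dec 2023: 346 days; 346 / 30.4375 = 11.4 months.
- From 31 Jan 2024: 285 days; 285 / 30.4375 = 9.4 months.

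**2. Sub-projects begun before or during t0.** Two started in December 2023 and January 2024 and two in 2024, so 2 + 2 = 4 of the 5 named. The months of the two 2024 starts are not given. Each fell either before 11 Nov 2024 or in the seven weeks to the end of that year, after t0 had opened. Only Evidence-based Nursing is clearly later.

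**3. Follow-up.** Six-month steps from November 2024 put t1 in May 2025 and t6 in November 2027, which fits the planned end of the first phase in 2027. So t0 is the only point before follow-up, and it serves as reference for all six contrasts.

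**4. What the contrast estimates.** Let e_k be the true effect at t_k against the never-exposed state, e₀ the effect already present at t0, and f the share of t0 measurements taken under exposure. Let m be the mean each group would have without exposure.

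- Intervention change: (m_I,k + e_k) − (m_I,0 + f·e₀)
- Control change: m_C,k − m_C,0
- With parallel trends, m_I,k − m_I,0 = m_C,k − m_C,0, so E[DiD_k] = e_k − f·e₀ and the bias is −f·e₀ at every k.

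**5. Illustration.** The values of e₀, f and e_k are assumptions, not in the article. Positive means better, in units of the outcome.

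| Effect at t0 (e₀) | True later effect (e_k) | DiD if f = 0.5 | DiD if f = 1 |
|---|---|---|---|
| −0.3 | 0 | +0.15 | +0.30 |
| −0.5 | 0 | +0.25 | +0.50 |
| +0.3 | +0.3 | +0.15 | 0.00 |
| 0 | +0.3 | +0.30 | +0.30 |

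The first two rows turn recovery from a dip into an apparent benefit. The third loses half or all of a real, lasting gain. The last shows that without an effect at t0 there is no bias, and that effects arising later are captured in full.

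**6. With a reference period before December 2023.** The effect in the reference period is then 0, so E[DiD_k] = e_k, provided trends are parallel over the longer span. For the publicly reported quality results, mandatory since 2022 and published twice a year (Summative evaluation), such a period exists. Routine data are kept by the homes in any case (Quality of care in nursing homes).

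**The case against.** The strongest reply is that a sub-project's start is not exposure on the ward. Of the first two sub-projects, one was to design and develop a learning infrastructure. The other is the coordination and evaluation centre, and Health economic evaluation classes overall evaluation as a study cost. Digitalization begins with selecting and testing. The transfer path tries innovations in one home before spreading them. Elsewhere the article speaks of the restructuring as still to come. The past tense about the TIAs is true at the time of writing and does not place them before 11 Nov 2024. The timetable figure (Fig. 2) is not visible here and may give dates. An article also condenses a fuller plan.

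Most of this stands, and it limits what can be said about size. It does not remove the point. The choice of t0 as sole reference is stated in the article, not left open. The TIAs are costed with the intervention, and Recruitment has them helping to enrol intervention residents, so their presence around the residents' t0 is plausible. If testing begins in one home, exposure at t0 may differ between homes, which makes home-level dates more necessary.

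Three stronger readings are tempting and not supported:

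- *That about a quarter of the effect is lost.* From 1 Dec 2023 to 31 Dec 2027 is 1,491 days, and 346 / 1,491 = 23%. Reading that as lost effect assumes full exposure from the first day, linear accrual and that end date. The text gives only months and a year, and linear accrual conflicts with the J-curve.
- *That every early effect is removed.* Only an effect present when t0 is measured is subtracted.
- *That job satisfaction or quality of care dips at t0.* The article states the possible worsening for sickness rate, turnover and agency use only.

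**Conclusion.** The concern holds as a directional risk, not as a demonstrated bias. The article anchors all outcomes at a t0 that opened 9.4 to 11.4 months after the first sub-projects started, overlaps or follows the start of two more, and had not closed at submission. Under parallel trends and unexposed controls, the bias in every contrast is −f·e₀. Its direction follows from the sign of the effect at t0: a dip inflates the apparent benefit, a gain hides it. Neither f nor e₀ can be derived from the text, and both could be near zero if little had reached the wards by then. As written, a reader cannot tell whether t0 is a baseline, and the control group cannot settle that.

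**What to change.** **Outcomes with a history.** For the publicly reported quality indicators and audits, and for home-level aggregate routine data (sickness rate, turnover, agency use, and counts of adverse events where the homes hold them), extract the periods before December 2023 from all six homes. Make these the reference of the difference-in-differences, treat t0 as a potentially exposed point, and report the t0-anchored estimate alongside.

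**Questionnaire outcomes, including job satisfaction.** These cannot be collected in retrospect. Record the date of each t0 response against each home's TIA start and first go-live. Use responses from before go-live as the reference where they exist. Otherwise report the estimate as change since t0 during implementation, not as the effect of the initiative.

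**Cost.** A longer look-back in an extraction that university staff already carry out, a dated record per home, and a sentence or two in Statistical analysis. Control homes are still being recruited, so look-back access can be agreed with them now.

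**Downsides.** Older records may be incomplete. Resident-level look-back is limited to residents who consent, which is why home-level aggregates are proposed. The years 2022 and 2023 also carry pandemic and staffing-policy effects, which the matched controls must absorb; showing both estimates lets a reader see how much depends on that.

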#### Data management

A comprehensive data protection concept has been developed and approved in advance by the legal office of the University of Bremen. It clarifies data processing, the rights of participants, and technical and organizational measures in order to ensure the secure and confidential collection, processing, and storage of data. Data is stored at the Competence Center for Clinical Trials Bremen which acts as a trust center. Access to pseudonymized data is limited to research staff from the University of Bremen and the City University of Applied Sciences in Bremen.

### Evaluation

#### Study design and participants

The basic methodology is a systemic evaluation approach [22], which combines both qualitative and quantitative research elements. The intended restructuring in the nursing homes can affect different, sometimes ethically relevant impact dimensions such as the quality of care for highly vulnerable people but also working conditions and processes. These dimensions will be captured using quantitative (standardized questionnaires) and qualitative methods such as focus groups and research diaries to gain further insights from residents, employees, nursing home management and TIAs concerning the implementation process of the several elements within the TCALL initiative (Fig. 4). For a successful implementation it is essential to fully understand rejecting or driving behaviors of all participating members in order to adapt the implementation process. This can lead to minor or major adaptions in single or multiple parts of the TCALL initiative. Additionally, qualitative methods support the participative, co-creative approach and will ensure that all participants (but especially the employees) feel valued and help changing and shaping the restructuring processes in nursing homes. In contrast to laboratory conditions, it is of great importance to address essential disruptive factors in everyday care immediately in order not to jeopardize the initiative and to keep employees and management motivated. An explanatory sequential mixed-methods design with an embedded quasi-experimental long-term study is used for the evaluation of this complex intervention to ensure that aspects of the quantitative results are interpreted correctly and to have reference points when contradictory results occur [23]. The study design also takes into account that confounding factors can influence the assessment of the outcomes. An important factor here has been the pandemic situation of the last few years, which has had a major impact on the care situation in LTC [24, 25] as well as changes in care policy, such as the implementation of new staffing ratios and their financing (Paragraph 113c of the German Social Code, Part 11). In order to avoid bias in the evaluation of the initiative, which may be associated with future changes, a matched control group is integrated into the evaluation.

The evaluation aims to measure the acceptance, effectiveness and efficiency of the TCALL initiative, thus providing internal quality assurance as well as external evidence of the added value of the TCALL initiative. In addition, initial approaches for dissemination and a sustainable nationwide rollout will be recorded.

The evaluation contains summative and formative components. The summative evaluation focuses on outcomes at two different levels: (i) employees and (ii) residents, with the most important outcome for employees being job satisfaction and for residents being quality of care. The formative evaluation aims to investigate the process of implementation of new structures, the acceptance of these structures and the achievement of goals for individual aspects in the TCALL initiative. Additionally, a health-economic evaluation with a cost-benefit analysis is planned.

**Fig. 4 Fig4:**
[figure not shown]
Quantitative and qualitative data

##### Eligibility criteria

Participants in this study can be either employees or residents in selected nursing homes (three ATNH and three matched controls). Inclusion criteria for employees is to have worked in the nursing home for at least four weeks prior to the start of the survey. This is intended to prevent positive and negative effects on the employees’ job satisfaction that may arise when starting a new job. No further exclusion criteria is used. Residents can participate in the study if the residents themselves or an authorized person (such as a legal guardian) confirm written informed consent. For ethical reasons care recipients at the end of their lives are excluded, and those who have been living in the nursing home for less than six weeks. This is due to the fact that a change of setting and living situation might have a positive or negative impact on the quality of life, depending on the previous situation at home.

##### Recruitment

Three nursing homes, which already report a high-quality standard and have a high and qualified staff ratio in order to avoid overloading of the nursing homes, have been selected to become the first ATNH (convenience sample). They were chosen as good and trustful relations with these nursing homes and their management already existed. The nursing homes are located in Bremen and are non-profit organizations. The nursing homes of the control group will be matched to the intervention group (number of beds, costs for residents and located in Bremen). The recruitment for the control group is ongoing.

Participation in the study is voluntary and based on written informed consent. Residents of the intervention group will be recruited by management, employees and TIAs. Management and employees of the intervention group have been informed in person at information events held by the study team in the participating nursing homes. The aim of these events was to inform management and staff of the nursing homes about the TCALL initiative and to enlist support from them. The control group will be recruited and informed by the scientific staff of the University of Bremen and the management of the control nursing homes.

